## Abstract

**Background:**

Population aging poses challenges to health systems and costs, and evidence shows that older adults spend a long time in ill health. Improving healthspan, time spent in good health, allows older adults to contribute and improve in their quality of life. Active and healthy aging are crucial to improving healthspan. Urban care farming (UCF) is a behavioral intervention that is purported to enhance active and healthy aging.

**Objective:**

This trial evaluates the effectiveness of a care farming intervention in improving the quality of life and biopsychosocial health outcomes of older participants.

**Methods:**

We conducted a parallel group, 2-arm pragmatic waitlist randomized trial with a 1:1 allocation, in which participants were randomized into either the intervention or waitlist control arm. Community-dwelling participants aged 50-85 years, without any mobility issues, were recruited. Participants in the intervention arm commenced the 24-week UCF program, while waitlist control participants received no intervention during this period. The primary (World Health Organization Quality of Life−brief version) and secondary outcomes were collected at baseline, 6th month, and 12th month after the intervention group completed the trial. Secondary outcomes include objectively measured physiological outcomes, cognition, frailty, and self-reported psychosocial outcomes. Intervention effects were estimated using mixed-effects difference-in-differences regression to account for repeated measurements.

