### Sample Size

This study aimed to compare the QOL between the treatment and waitlist control participants, using a 1:1 allocation ratio. Based on a prior study of the overall WHOQOL measure, if the true difference-in-differences estimate between experimental and control means is 4.93 with a standard deviation of 9.29 [46], a sample of 57 intervention and 57 control subjects is required to reject the null hypothesis based on a 2-tailed significance level of 5% and power of 80%. We inflated the sample by 20% to account for dropouts and the potential loss of participants due to noncompliance and faulty measurements. Accounting for all these factors, the total sample size required for 2 arms is 138 participants.

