#### Statistical Analysis

The primary analysis, intention-to-treat, will be conducted using a linear mixed effects model with overall WHOQOL score as the dependent variable and the interaction effect of intervention allocation and time as the independent variable. Domain-specific scores will also be analyzed. To address potential bias arising from missing data due to attrition or incomplete responses, our primary longitudinal analyses will employ linear mixed-effects models, which are robust to unbalanced data structures and can handle missing observations under the missing-at-random assumption. While listwise deletion may be used for cross-sectional comparisons or descriptive analyses, this will be clearly indicated. Secondary outcomes will be analyzed using similar methods. These analyses will be conducted at 6-month follow-up to investigate the effectiveness of the intervention as well as post-intervention behavioral maintenance at 12 months. Sensitivity analysis using the per-protocol approach will also be carried out. Baseline characteristics of participants who discontinued or were lost to follow-up will be compared to those who completed the study to investigate differential dropout between intervention and control groups.

Due to potential imbalances between the groups, further analysis techniques, such as adjustment or matching of baseline characteristics, will be used in the difference-in-difference analysis. Specifically, we will adjust or match on key baseline covariates (eg, age, gender, years of education, marital status, and housing type) to improve group comparability at baseline in case of any imbalance despite randomization. This approach improves covariate balance and enhances the comparability of groups prior to applying linear mixed models for outcome analyses. Conducting both intention-to-treat and per-protocol analyses for this behavioral intervention allowed comparison of the results and provided a comprehensive understanding of the treatment effect. All evaluations were and will be performed using a 2-sided test at the 5% level of significance.

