Nevertheless, this study has several limitations. The effect size used for sample size estimation was based on a prior WHOQOL study, which may not fully reflect the characteristics of the Singaporean older population or the unique aspects of the UCF intervention. The calculated sample size also includes a 20% buffer to account for expected attrition in long-term community interventions. Sensitivity analyses for secondary outcomes were not included. One methodological challenge is estimating the effect sizes of repeated measures data. To address this, the study will employ linear mixed-effects models and robust standard errors to derive reliable difference-in-difference estimates. This statistical approach enables the evaluation of longitudinal data, accounting for within-subject correlation and heterogeneity in responses over time. Attrition over the 24-week period may limit the ability to evaluate longer-term outcomes, though mitigation strategies such as regular participant engagement and reminders have been implemented. Next, the use of self-reported measures may introduce recall and reporting bias; however, the inclusion of biomarkers and clinical assessments partially mitigates this. Finally, the findings may be less generalizable to more frail or homebound populations, as the study sample consists of relatively healthy, community-dwelling individuals who are able to travel and commit to a 24-week intervention. As such, the study sample is likely skewed toward relatively healthy and motivated individuals, which may limit the generalizability of our findings. While the results offer important insights into the potential benefits of urban care farming, future work should explore adaptations of the intervention to accommodate more vulnerable older adults and assess its effectiveness in those populations. For future trials, we also recommend a more structured approach to adverse event monitoring, including standardized incident reporting forms and real-time logs, to further strengthen safety assurance and protocol reproducibility.

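### The primary difference-in-differences is unbiased but inefficient: constraining the randomised arms to a common baseline mean (or ANCOVA) targets the same 6-month effect with variance lower by (1−ρ)/2

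*Protocol article*

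**What the plan says.** Four places in the protocol article fix the choice, and they agree.

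- Statistical Analysis: the model for the primary intention-to-treat analysis is given as "linear mixed effects model with overall WHOQOL score as the dependent variable and the interaction effect of intervention allocation and time as the independent variable". Secondary outcomes are to be handled similarly.
- Abstract, Methods: "Intervention effects were estimated using mixed-effects difference-in-differences regression to account for repeated measurements".
- Sample Size: the trial is sized "if the true difference-in-differences estimate between experimental and control means is 4.93 with a standard deviation of 9.29", two-sided 5% level, 80% power, giving 57 per arm and 138 in total after a 20% inflation.
- Discussion, limitations: "the study will employ linear mixed-effects models and robust standard errors to derive reliable difference-in-difference estimates".

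Statistical Analysis also provides for adjustment or matching if the groups turn out to be imbalanced, on "key baseline covariates (eg, age, gender, years of education, marital status, and housing type". Baseline WHOQOL is not named there. No section plans a common baseline mean for the two arms or an ANCOVA on the baseline score.

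Blinding and Assignment of Groups says that allocation was disclosed at the last station, after consent and all baseline measurements. Results gives 137 enrolled (67 and 70) and says that analysis of the baseline and 6-month data is in progress.

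**The concern.** In an arm-by-time model with an allocation main effect and complete data, the 6-month interaction equals the difference between arms in mean change. The baseline score is subtracted with coefficient 1, whatever its correlation with the 6-month score. That is reasonable when groups may truly differ at baseline, as in observational work. Here the arms were formed by randomisation and baseline was measured before anyone knew the allocation, so the true baseline difference is zero by design. Estimating it and subtracting it in full brings in sampling error that the design does not require.

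There are two consequences. The primary estimate has a larger variance than it needs for any correlation below 1. And if the arms differ at baseline by chance, the estimate over-corrects: the arm that happened to start lower tends to show the larger gain through regression to the mean. With enrolment closed at 137, the analysis is the main remaining place where precision on the primary outcome can be gained.

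**Working it through.** **Inputs from the protocol article (Sample Size, Results).** Difference-in-differences Δ = 4.93; SD 9.29; two-sided α 0.05; power 80%; 57 per arm; 20% inflation; 138 in total; 67 and 70 enrolled.

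**Assumed.** ρ, the correlation of WHOQOL between baseline and 6 months, is not given and is shown as a range. SDs are taken as equal at both visits and in both arms.

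**1. The plan's own figure.** Normal approximation: n = 2 × [9.29 × (1.960 + 0.842)/4.93]² = 55.7, so 56 per arm. The t-test version gives 56.7, so 57. Then 57 × 1.2 = 68.4, rounded up to 69 per arm, or 138. The stated figures reproduce. Noncentral t power at 57 per arm is 80.2%.

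**2. Variance with complete data.** Let s be the SD of the score. The per-participant variances are:

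- Change score (difference-in-differences): 2s²(1−ρ)
- Common baseline mean or ANCOVA: s²(1−ρ²)
- Ratio: (1−ρ²)/[2(1−ρ)] = (1+ρ)/2
- Saving: 1 − (1+ρ)/2 = (1−ρ)/2

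**3. Variance with a fraction m seen at 6 months.** A likelihood-based mixed model keeps participants who have baseline only. Per arm:

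- Difference-in-differences: proportional to (1−ρ²)/m + (1−ρ)²
- Common baseline mean: proportional to (1−ρ²)/m
- Ratio: (1+ρ)/[(1+ρ) + (1−ρ)m]

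For ρ = 0.5 and m = 0.8 this is 1.5/(1.5 + 0.4) = 0.789, a saving of 21%.

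| ρ | Saving, complete data | Saving, 20% missing at 6 months |
|---|---|---|
| 0.3 | 35% | 30% |
| 0.5 | 25% | 21% |
| 0.6 | 20% | 17% |
| 0.7 | 15% | 12% |
| 0.8 | 10% | 8% |
| 0.9 | 5% | 4% |

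**4. Simulation (67 vs 70, no true effect, 20,000 replicates).** Both estimators averaged zero to within 0.001 SD. The variance ratios were 0.76 (ρ 0.5) and 0.86 (ρ 0.7) with complete data, and 0.80 and 0.88 with 20% missing at random. The formulas give 0.75, 0.85, 0.79 and 0.88. The small excess is the price of estimating the slope.

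**5. Power at 57 per arm, Δ = 4.93, complete data (noncentral t).** Sample Size does not say whether 9.29 is the SD of change or of the score, so both are shown.

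| ρ | If 9.29 is the SD of change: planned → adjusted | If 9.29 is the SD of the score: planned → adjusted |
|---|---|---|
| 0.5 | 80% → 90% | 80% → 90% |
| 0.6 | 80% → 88% | 88% → 94% |
| 0.7 | 80% → 86% | 95% → 98% |

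In the first case the adjusted SD is 9.29 × √[(1+ρ)/2]. In the second, the planned SD is 9.29 × √[2(1−ρ)] and the adjusted SD is 9.29 × √(1−ρ²).

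**6. Chance imbalance.** Given an observed baseline difference d, the expected 6-month difference is the true effect plus ρd. Subtracting d in full leaves the true effect minus (1−ρ)d. Averaged over randomisations d is zero, so there is no bias overall. In the one trial actually run, the displacement is (1−ρ)d.

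**The case against.** The strongest reply is that nothing here is wrong. The difference-in-differences is unbiased under randomisation, the trial was sized on that same contrast, and the sample size reproduces. This stands: a reader might infer that the primary estimate is biased or that the trial is underpowered by its own reckoning, and the article supports neither. Unbiasedness does not remove the loss of precision, however.

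A second reply is that the model form is inferred, because Statistical Analysis names only "the interaction effect of intervention allocation and time as the independent variable" and does not say whether an allocation main effect is included. If it were left out, the arms would already share a baseline mean. That is possible, but the repeated difference-in-differences label, including the Discussion's intention to "derive reliable difference-in-difference estimates", makes the usual form with separate baseline means the natural reading.

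A third is that the covariate list is open-ended and that baseline WHOQOL already enters the mixed model as a repeated outcome. Both are true. But the adjustment applies only in case of imbalance, and having baseline as an outcome with arm-specific means is exactly what produces the full subtraction.

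A reader might also take 15% to 25% as the established saving. It needs ρ between 0.5 and 0.7 and complete follow-up, and the article gives no ρ. Nor can it be said that the gain would make up for attrition or for any clustering by session group: the article gives no intraclass correlation, and dropout already has its own 20% allowance.

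Finally, the change is not free of procedural cost. Outcome data exist and analysis is under way, so changing the primary estimator now needs a dated justification. This stands and is built into the fix.

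**Conclusion.** The concern holds as a point of efficiency, not validity. The planned primary contrast gives up a fraction (1−ρ)/2 of its variance, under equal SDs and complete data, for any ρ below 1. Across ρ from 0.3 to 0.9 that is 35% down to 5%. For ρ from 0.5 to 0.7 it is 25% to 15%, or about 21% to 12% with 20% missing at 6 months.

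If 9.29 is the SD of change, power at 57 per arm would rise from 80% to about 90% (ρ 0.5) or 86% (ρ 0.7). If it is the SD of the score, the gain is about 10 points at ρ 0.5, 6 at 0.6 and 2 at 0.7. The direction of the gain does not depend on ρ or on the meaning of the SD; its size depends on both. The conclusion rests on reading the difference-in-differences model as having arm-specific baseline means, which the article implies but does not spell out. The change should be made, but the planned analysis would not be invalid without it.

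**What to change.** Make one of these the primary analysis of overall WHOQOL:

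- a linear mixed model with categorical time and allocation × 6-month and allocation × 12-month terms, but no allocation main effect at baseline, keeping every participant with at least one visit; or
- ANCOVA of 6-month WHOQOL on baseline WHOQOL and allocation.

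Use the same form for the domain scores and for secondary outcomes that have a baseline measurement. Keep the difference-in-differences estimate as a sensitivity analysis, so that the link to the sample-size calculation stays visible. If the intended model already has no allocation main effect at baseline, one sentence saying so settles the point.

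The cost is one model term, one sentence in the plan and about one degree of freedom. No new data are needed and the 6-month effect being estimated is unchanged. Because follow-up is complete and analysis is ongoing, record the change with a date and a reason, state what had been seen by then, and do this before any treatment-effect result is examined. If such results have already been seen, report both estimates and say so.

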**Results:**

The randomized controlled trial commenced in April 2024, with the intervention group starting first. By April 2024, we had enrolled 137 participants at commencement, with 67 participants randomized to the intervention group and 70 to the control group. The intervention arm started in April 2024 and concluded in September 2024. Baseline data were collected in March 2024, and 6-month follow-up data were collected in September 2024. The waitlist control participants began the UCF intervention at the end of September 2024 and concluded in April 2025. Data collection for the 12-month follow-up concluded in May 2025. Analysis of the baseline and 6-month follow-up data is still ongoing.

**Conclusions:**

The outcomes of this study will contribute to the understanding of UCF on quality of life and health. This trial has potential positive implications for public health, as it utilizes a robust research design and methods to provide empirical insights into the multifaceted health benefits of the multicomponent UCF intervention. This trial could also serve as a model for future intervention research on scalable, community-based programs. Taken together, the UCF content and the outcomes, process, and economic evaluations completed through this study could inform scalable models of the UCF intervention, with potential implications for public health strategies to address health issues related to population aging.

## Introduction

Globally, population aging has raised concerns about the growing burden on health care systems and rising health care costs. While life expectancy has increased, individuals are living longer in poorer health [1]. Aging brings about physiological changes, such as the loss of muscle mass, which leads to functional decline and reduced brain volume [2,3], contributing to cognitive impairment [4]. Emotional and psychosocial well-being are also impacted, with older adults experiencing higher rates of depression [5] and social isolation [6]. In Singapore, 1 in 5 older adults aged 75 years and above shows signs of depression [7], and the proportion who committed suicide rose from 23% in 2000 to 30% in 2014 [8]. Furthermore, many mental health conditions remain underdiagnosed and untreated, largely due to stigma and delayed health-seeking behavior [9]. Active and healthy aging are crucial to improving healthspan. Care farming is a behavioral intervention that is purported to enhance active and healthy aging.

Care farming is a nature-based therapeutic intervention that integrates agricultural and farming practices to positively influence participants in multiple health domains [10-12]. Nature-based intervention (NBI) has garnered traction as a green social prescribing activity that addresses upstream social determinants of health [13]. The nature-based biopsychosocial resilience theory (NBRT) provides a conceptual foundation for understanding how exposure to nature can promote health and well-being [14]. The NBRT posits that humans have an inherent affinity for the natural environment, through which they derive restorative benefits that support biopsychosocial resilience and overall health. According to White and colleagues, biopsychosocial health restoration occurs through increased exposure to nature, which reduces stress (eg, by mitigating pollution through the use of trees) while simultaneously strengthening resources such as physical fitness, social connections, and self-esteem. The NBRT also aligns with the World Health Organization’s quality of life (QOL) definition, which emphasizes health and illness as outcomes of complex interactions among biological, psychological, and social factors.

The World Health Organization defines QOL as an individual’s perception of their position in life, considered within the context of their culture, values, goals, expectations, standards, and concerns [15]. To capture this multidimensional construct of health, the WHOQOL (World Health Organization Quality of Life) instruments assess multiple domains, including physical, psychological, social, and environmental aspects of well-being. From this perspective, a comprehensive understanding of a person’s health or QOL requires the consideration of biological processes and lifestyle; cognitive and emotional functioning; coping capacities; and the social context of relationships, support systems, and culture. Given the multidimensional nature of WHOQOL, its domains align closely with the components of the NBRT, offering a coherent framework for evaluating health and well-being. In line with this, active aging aims to maintain functional ability, promote participation, and enhance the QOL as people age [16,17].

Growing evidence suggests that adopting healthy behaviors can lower disease risk, enhance physical and mental health function, and delay the onset of care dependency [18]. Care farming is valued for its multidimensional impact on biopsychosocial health and QOL. It is an intervention with the goal of promoting holistic health through activities by increasing light-to-moderate physical activity; reducing stress, anxiety, and negative mood; enhancing positive mood; fostering social interaction and sense of purpose; stimulating cognition; and encouraging healthier eating habits [19-24]. Unlike many NBIs, which can be undertaken individually, care farming places a stronger emphasis on fostering community engagement and collaboration. Hence, we hypothesize that care farming better addresses psychological and social relationship domains of QOL by fostering a sense of purpose and social connectedness through collective cultivation, responsibility, and group harvesting and communal cooking. Care farming is therefore a highly complex intervention consisting of interrelated components that target multiple domains of well-being. This is consistent with the UK Medical Research Council’s framework for complex interventions, which considers the interaction of multiple components, variability in outcomes, and context-sensitive implementation [25].

Although care farming is garnering attention as a green care intervention, the empirical evidence remains limited. Systematic reviews by Murray et al [12] and Coventry et al [26] highlight limitations in current literature, concluding that there is mixed evidence showing that care farming or NBIs improved individuals’ health, well-being, and QOL. Murray et al also found that only 2 care farming studies employed randomized controlled methods, with the majority of reviewed studies being pre-post and qualitative studies conducted with small sample sizes. Moreover, care farming tasks are typically tailored to the needs and capabilities of participants, shaped by the type of farm and the resources available. Such flexibility poses challenges for research, as the heterogeneity of care farming interventions complicates the identification of mechanisms of change and limits both replicability and generalizability. Both reviews also noted that care farming is grouped with other NBIs, making it difficult to attribute observed outcomes specifically to farming-related activities. These limitations underscore a clear literature gap and the need for a robust, well-designed experimental study with structured tasks to establish the effectiveness of care farming as a health intervention.

There is a strong theoretical and empirical rationale to assess its potential impacts across physical, psychological, cognitive, and behavioral domains. This study aims to (1) develop a structured care farming intervention, which we termed urban care farming (UCF) and (2) evaluate the acceptability and effectiveness of a structured UCF program for older adults in Singapore using a waitlist randomized controlled trial. Specifically, this outcome evaluation seeks to answer the following research questions:

Effectiveness on primary outcome: Does participation in UCF improve overall QOL, as measured by the WHOQOL-BREF (World Health Organization Quality of Life−brief version), relative to a waitlist control?Effects on secondary and exploratory outcomes: What are the effects of UCF on physical activity, psychosocial well-being, dietary behaviors, cognitive function, and biomarkers?

These research questions were guided by the intervention’s logic model (Figure S1 in Multimedia Appendix 1), which outlines hypothesized pathways from program activities to short- and medium-term outcomes. This intervention targets multiple dimensions of health, including physical, psychological, social, and cognitive outcomes, aligning with both the WHOQOL framework and biopsychosocial model [27,28]. In addition, subsequent, separate evaluations of UCF will also incorporate process and cost-effectiveness assessments to further examine implementation effectiveness and identify challenges. These evaluations include the following:

Process evaluation will be conducted to assess the quality of urban care farming (UCF) intervention delivery, including fidelity, dose delivered and received, acceptability, and to identify the mechanisms and contextual factors that facilitate or hinder outcomes.Cost-utility analysis will be conducted from the provider and societal perspective to assess the potential value of scaling up the UCF intervention, using quality-adjusted life years (QALYs) as the primary effectiveness metric. This economic evaluation will be exploratory in nature and designed to inform future trial design and policy translation.

